#### Adherence to and tolerance of the prescribed cycle ergometer exercise

Physical therapists will record for every cycle ergometer exercise session if patients exercised at all (yes or no), the performed workload (in Watts), if patients reached the target workload (in Watts), adjustments of workload and the requirement for oxygen. We define adherence to exercise as "full adherence" if patients follow at least 12 exercise sessions. We consider the training to be fully tolerated if patients are able to follow the exercise protocol for at least 9 exercise sessions for continuous exercise (taking into consideration the first three exercise session when patients increase training load up to 70% of maximum exercise capacity) and for at least 12 exercise sessions for interval exercise.

#### Adverse events

Previous trials of respiratory rehabilitation or physical exercise did not report any adverse events. Nevertheless, we will record any adverse events such as injuries, cardiac events or increase of respiratory symptoms as they happen during the inpatient respiratory rehabilitation.

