**Methods/Design:**

We will assign patients with moderately severe to severe COPD to either continuous exercise or interval exercise using a stratified randomisation. Patients will follow 12–15 exercise sessions during a comprehensive inpatient respiratory rehabilitation. Primary end point for effectiveness is HRQL as measured by the Chronic Respiratory Questionnaire (CRQ) two weeks after the end of rehabilitation and secondary endpoints include additional clinical outcomes such as functional exercise capacity, other HRQL measures, patients' experience of physical exercise as well as physiological measures of the effects of physical exercise such as cardiopulmonary exercise testing. Including expected drop-outs, we will need 52 patients per group to show differences corresponding to the minimal clinically important difference of the CRQ. Outcome assessors and investigators involved in data analysis will be blinded to group assignment until analyses have been carried out.

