## Methods

### Study design (see figure 1)

**Figure 1 F1:**
[figure not shown]
Flow of the study from screening for eligible patients to the final outcome assessment.

All consecutive patients admitted to a teaching rehabilitation clinic for an inpatient respiratory rehabilitation (Klinik Barmelweid, Barmelweid, Switzerland) will be assessed for study eligibility by senior staff physicians. If patients are deemed eligible after exercise testing, which is part of the usual rehabilitation program, senior physicians will inform patients about the study orally and in writing. If patients are willing to participate and provide written informed consent they will be randomly assigned to respiratory rehabilitation with either interval or high intensity continuous exercise. Both groups will perform 12–15 exercise sessions and follow the rest of the rehabilitation programme. Follow-up assessments will be done during, at the end of the rehabilitation programme as well as two and twelve weeks afterwards when patients are back in their home environment.

The Ethikkommission of the Kantonsspital Aarau, Aargau, Switzerland, has approved the study protocol.

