### Randomisation

A third party not involved in the conduction of the trial will provide online central randomisation (DatInf GmbH, Tuebingen, Germany). A computerised 'minimisation' procedure will be used to avoid chance baseline imbalances in prognostically important variables[21] Minimisation variables will be exercise capacity (< 300 or ≥ 300 meters in six-minute walk test), the presence of affective disorders (Hospital Anxiety Depression Scale scores < or ≥ 8), status of COPD (unstable COPD = In- or outpatient medical care in the last eight weeks due to exacerbation of COPD versus stable COPD = no in- or outpatient medical care in the last eight weeks due to exacerbation of COPD) and the need for oxygen at rest (yes = long term home oxygen therapy or paO_2 _< 55 mmHg or no = paO_2 _≥ 55 mmHg).

Every time the study coordinator has been informed about an enrolled patients, he will enter the randomisation web site[22] enter the patient data required for randomisation (patient identification and stratification variables) and obtain group allocation. The study coordinator will then inform responsible physical therapists about group allocation. No other medical staff will have knowledge about group allocation. The randomisation provider will also send an e-mail to the study coordinator for each randomised patient with details on randomisation. This will ensure correct verification of group allocation after data analysis.

Separating patient enrolment and baseline assessments (physicians and physical therapists) from the randomisation procedure (study coordinator not involved in patient enrolment or rehabilitation programme) will ensure concealment of random allocation.

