### Interventions

The rehabilitation programme will start one day after baseline assessments and study enrolment. Exercise sessions and group lessons will take place five days a week and will consist of daily cycle ergometer training, breathing therapies (30 minutes per day), and guided walking of 15 to 30 minutes. Relaxation therapies (technique according to Jacobson) take place twice a week, patient education (information about COPD, coping strategies, inhalation techniques) three times a week, smoking cessation advice once a week or more if needed. Apart from physical exercise, the rehabilitation programme of approximately three weeks will be identical for both groups.

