### Data collection and quality control

We will implemented a series of measures to ensure high data quality.

1. Site investigators will collect the data using standardized forms. All data will be collected and entered into a single database in the Horten Centre by one investigator. A second investigator will validate completeness and accuracy of data extraction by checking 20% of extracted patient data.

2. Checklists with all the data to be collected will be provided for physical therapists and physicians.

3. Teaching sessions will be held regularly for physical therapists and physicians involved in data collection aiming at robust data collection.

4. Investigators meetings will be held monthly, or more frequently if needed, to discuss recruitment of patients, problems in conducting the study, acquisition of data, to check for consistency and completeness of data and for interim analyses.

5. E-mail will serve as the first line of non-urgent communication between research team members.

6. Monthly reports will be prepared by the principal investigator that will include the number of patients recruited, stage of follow up for each patient, notification regarding missing patient data and queries from data received.

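### Adverse event recording is tied to the inpatient stay of about three weeks, although the primary endpoint is two weeks later and follow-up runs to week 12 (minor)

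*Protocol article*

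**What the plan says.** Under Monitoring of exercise sessions, the Adverse events section states both the events and the period: the investigators will "record any adverse events such as injuries, cardiac events or increase of respiratory symptoms as they happen during the inpatient respiratory rehabilitation". The Interventions section gives the length of that stay: apart from the exercise itself, "the rehabilitation programme of approximately three weeks will be identical for both groups".

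Follow-up goes on after discharge. The abstract names as primary endpoint the "Chronic Respiratory Questionnaire (CRQ) two weeks after the end of rehabilitation", and the Study design section places further assessments at the end of the programme "as well as two and twelve weeks afterwards when patients are back in their home environment".

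The article itemises what is collected after discharge: the CRQ, the Hospital Anxiety Depression Scale (HADS) and the Feeling Thermometer at 2 and 12 weeks, the six-minute walk test at 2 weeks, and smoking status at both time points.

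Exacerbation is a defined data item in one place only, the Randomisation section, where it sets a minimisation factor at entry: "unstable COPD = In- or outpatient medical care in the last eight weeks due to exacerbation of COPD".

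**The concern.** The stated window closes before the primary endpoint is measured. The plan itself treats a recent exacerbation as prognostic: it minimises on it, and the section on confounders describes the minimisation factors as likely to influence the outcomes. The patients have GOLD stage III-IV disease. An exacerbation or admission in the two weeks after discharge could lower a patient's CRQ score and walking distance, or be the reason they are missing.

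If such events are not recorded, two things are lost. The first is a comparison of harms by arm over the whole follow-up. The second is an account of why a two-week score is low or absent. The plan allows for 15% drop-out, so the second question will probably arise.

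**Working it through.** The plan gives no figure for adverse event coverage, so there is none to reproduce. The check sets the recording window beside the follow-up schedule.

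**1. Inputs**
- Inpatient stay: about 3 weeks (Interventions).
- Primary endpoint: 2 weeks after the stay (Abstract; Effectiveness).
- Last assessment: 12 weeks after the stay (Study design).
- Event window: the inpatient stay (Adverse events).

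**2. Calendar coverage**
- Programme start to primary endpoint: 3 + 2 = 5 weeks. Covered 3/5 = 60%, uncovered 2/5 = 40%.
- Programme start to last assessment: 3 + 12 = 15 weeks. Covered 3/15 = 20%, uncovered 12/15 = 80%.

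These are shares of time. They measure neither missed events nor bias in the CRQ.

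**3. Is there another route by which events are captured?** The sections on CRQ, HADS, Feeling Thermometer, walk test and additional data together list what is taken after discharge. None includes an adverse event, exacerbation, admission or cardiac event. A later exacerbation might show indirectly as a worse score, but not as an event.

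**4. Possible number of events.** The document gives no exacerbation rate. As an assumption, take 0.5 to 3 per patient-year, with expected events = patients × rate × weeks/52.

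| Period after discharge | 104 patients (no drop-out) | 88 patients (2 × 44 completers) |
|---|---|---|
| To week 2 (primary endpoint) | 104 × 0.5 × 2/52 = 2.0 to 104 × 3 × 2/52 = 12.0 | 1.7 to 10.2 |
| To week 12 (includes weeks 1-2) | 104 × 0.5 × 12/52 = 12.0 to 104 × 3 × 12/52 = 72.0 | 10.2 to 60.9 |

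The counts are for both arms together and say nothing about imbalance between them.

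**5. Effect on sample size.** The plan's formula with difference 0.5, SD 0.8, one-sided 5% and 90% power gives n = (1.645 + 1.282)² × 2 × 0.8² / 0.5² = 43.9, so 44 per group. With 15% drop-out, 44/0.85 = 51.8, so 52 per group and 104 in total. Both stated figures reproduce. No term in the formula depends on the event window, so extending it changes nothing here. The difference 104 − 88 = 16 is the number of drop-outs the plan allows for.

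**The case against.** **The window matches the exposure.** The randomised difference is 12 to 15 supervised cycling sessions, all during the stay, and the article describes no trial exercise afterwards. Recording harms while the exercise is given is coherent and contradicts nothing else in the article. This stands, and it is a main reason why the point is minor.

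**The article does not say that recording is limited to the stay and nothing else.** The limit follows from the stated period and from the absence of events among the listed post-discharge items. A fuller protocol or the case report forms might collect more. This lowers confidence but does not remove the point, because the article is not silent: it names a window, and that window is shorter than its own follow-up.

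**The primary comparison does not need these data.** A reader might infer that unrecorded exacerbations undermine the non-inferiority result because training effect and exacerbation cannot be separated. The documents do not support that. Exacerbations unrelated to arm are balanced in expectation by randomisation, helped by minimisation on recent exacerbation. Those caused by an arm are part of the effect being compared. Adjusting for an event after randomisation could itself introduce bias.

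**Two further inferences should not be drawn.** The Discussion mentions benefit and downsides of exercise protocols, but in a sentence about how few pragmatic trials exist so far; it is not a planned safety conclusion. The monthly report is said to include recruitment numbers and "stage of follow up for each patient, notification regarding missing patient data and queries from data received". That list is not stated to be exhaustive, so the absence of adverse events from it shows nothing.

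**Conclusion.** The point holds as a minor one. The stated window leaves about 2 of the 5 weeks to the primary endpoint, and about 12 of the 15 weeks to the last assessment, without planned event recording. Under the assumed rates of 0.5 to 3 per patient-year and 104 patients, about 2 to 12 exacerbations before the primary endpoint and 12 to 72 by week 12 would fall outside it.

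The loss is in harms data by arm after discharge and in explaining missing or low CRQ and walk-test values at two weeks. The intention-to-treat contrast, sample size and alpha are untouched, and no bias has been shown.

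The conclusion rests on the stated programme length of about three weeks, on reading the listed post-discharge items as the planned ones, and, for the event counts only, on the assumed rates.

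**What to change.** Extend event recording to the 2-week and 12-week assessments that already take place:

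- Reuse the exacerbation item from the Randomisation section, with the eight-week look-back replaced by the time since the last assessment.
- Add hospital admission, cardiac event and death, each with its date.
- Report these events by arm, separately for the stay, weeks 1-2 and weeks 3-12 after discharge.
- Use them descriptively to classify the reasons for missing CRQ scores. State that the primary comparison will not be adjusted for them, since they arise after randomisation.

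The cost is a few questions at two existing contacts, with no change in sample size. The downside is that these events would be self-reported by patients who know which training they had. The ten weeks before the 12-week contact (12 − 2 = 10) are a long recall period, and no walk test is planned at that contact. Reported admissions and cardiac events would therefore need some checking.

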### Cardiopulmonary exercise testing

At baseline and end of the rehabilitation, all patients will perform an incremental cycle ergometer test to the limit of tolerance (symptom based) under the supervision of a senior physician blinded to group assignment. Patients pedal unloaded for three minutes to warm up at 20 Watts. Then exercise load is increased by 7.5 Watts per minute until patients have to stop because of dyspnoea, leg pain, or criteria for stop testing (atrial or ventricular tachycardia, ischemia, hypoxemia). At the limit of tolerance, we will draw capillary blood samples to measures lactate concentrations and we will set the maximum exercise capacity expressed by Watts. The upper limit for the heart rate during exercise is set as the heart rate measured by the electrocardiogram at the maximum exercise capacity.

During testing, we will record gas exchange and ventilatory variables form calibrated signals derived from rapidly responding gas analyzers and a mass flow sensor. We will record breath by breath the following variables: Pulmonary oxygen uptake, pulmonary CO_2 _output, minute ventilation, tidal volume and respiratory frequency.

All patients will perform a steep ramp test at the beginning and end of the rehabilitation programme as described above.

#### Additional data to be collected

In order to characterize the patient included in the study, we will record their age, gender, lung function (FEV1, FEV1/FVC, diffusion capacity DLCO/VA, weight, height, smoking status at the beginning and end of rehabilitation as well as two and 12 weeks afterwards, duration of disease (time since diagnosis), co-morbidities such as hypertension, heart diseases, endocrine disorders, chronic rheumatological disorders and psychiatric disorders.

### Data analysis

The randomisation code will not be broken (investigators remain blinded to group assignment and will receive only codes, such as group 1 and 2) until a draft of the manuscript has been written. The authors will write two versions with alternative possible allocation patterns to avoid bias in the interpretation of the results. This approach is methodologically rigorous and limits introduction of bias during the interpretation of the data that some of the authors might have.[38] We will submit the appropriate manuscript regardless of the results of unmasking. After agreement on the final versions of the two articles, we will break the randomisation code and we will submit the correct version of the manuscript.

### Effectiveness

Our null hypothesis is that high intensity continuous exercise is of clinically superior effectiveness compared with interval exercise to improve HRQL (δ ≥ 0.5 in CRQ domains scores). The alternative hypothesis is that interval exercise is not of clinically inferior effectiveness compared with high intensity continuous exercise.

In the primary analysis, we will calculate the raw difference and 95% confidence intervals between groups in the mean follow-up score for the CRQ domains 2 weeks after completion of the respiratory rehabilitation programme. In an additional analysis, we will adjust for the base-line score and the four stratification variables using an analysis of covariance. We will use independent t-test to compare the change scores between groups.

We will also use the confidence interval approach as recommended for equivalence and non-inferiority trials[13] We will establish non-inferiority of interval exercise if the point estimate and its 95% confidence interval for difference between the change scores of the continuous and interval exercise group is smaller than the a priori determined boundary of clinical equivalence (see figure 3). If the 95% confidence intervals lie outside the boundaries of clinical equivalence we will establish clinical superiority of one exercise protocol.

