**Figure 3 F3:**
[figure not shown]
Illustration of the confidence interval approach to interpret results from randomised trials. The horizontal line indicates the difference between CRQ change scores between study groups. ± 0.5 points represent the predefined boundaries of equivalence. If the whole confidence interval is on the right of 0.5 points, interval exercise is not inferior to continuous exercise. If the whole confidence interval is within boundaries the two exercise protocols are of clinically equivalent effectiveness (upper three confidence intervals). Note that there can be a statistically significant difference between study groups but without any clinical relevance.

Most methodologists and statisticians agree that the boundaries of equivalence should be defined as the minimal important difference and below the differences observed in previous trials comparing active to control treatments.[13,39] The minimal important difference is "the smallest difference in score in the outcome of interest that informed patients perceive as important, either beneficial or harmful, and which would lead the clinician to consider a change in the management"[40]. Therefore, the minimal important difference of our two main outcome measures for effectiveness have been established empirically and are around 0.5 for the CRQ domains scores [41-44] and 53 meters for the six-minute walk test[45]. A recent meta-analysis showed that respiratory rehabilitation with physical exercise leads to improvements of 50 meters in the six-minute walk test. Therefore we lower the boundaries for equivalence to ± 45 meters in order to have boundaries that are below the differences observed in previous trials comparing active to control treatments.[13,39]

We will repeat the analysis with calculations of raw and adjusted differences for all other clinical and physiologic outcome measures and test for significant differences between groups using independent t-test if data are distributed normally.

We will use both intention to treat and per protocol analysis to show equivalence in either case as recommended by others[13,39,46,47]

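### The analysis labelled primary (raw follow-up difference) is not the one that decides non-inferiority (change scores), and the more precise ANCOVA is only additional

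*Protocol article*

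**What the plan says.** The protocol article's Effectiveness section plans three estimates of the same treatment effect on the CRQ:

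- **Raw follow-up difference**, which carries the primary label: "we will calculate the raw difference and 95% confidence intervals between groups in the mean follow-up score". It is taken two weeks after rehabilitation ends, on each CRQ domain.
- **ANCOVA**, as a supplement: "In an additional analysis, we will adjust for the base-line score and the four stratification variables using an analysis of covariance".
- **Change scores**, as the test: "We will use independent t-test to compare the change scores between groups".

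The next paragraph of that section bases the non-inferiority decision on the third of these. The criterion is that the "95% confidence interval for difference between the change scores of the continuous and interval exercise group is smaller than the a priori determined boundary". The Figure 3 legend uses the same scale ("The horizontal line indicates the difference between CRQ change scores between study groups") and gives the margin: ± "0.5 points represent the predefined boundaries of equivalence".

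On allocation, the Randomisation section says: "A computerised 'minimisation' procedure will be used to avoid chance baseline imbalances in prognostically important variables". The four factors are six-minute walk distance, HADS score, COPD stability and oxygen need. Baseline CRQ is measured but is not among them.

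**The concern.** The primary objective is non-inferiority, yet the estimate called primary does not appear in the rule that settles it. The rule is introduced as something done in addition to the primary analysis, and no sentence ranks the two. If one interval clears 0.5 and the other does not, the authors must choose after seeing the results.

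Precision is also at stake. Neither the raw nor the change-score comparison makes best use of baseline CRQ, and neither includes the four minimisation factors. Leaving out prognostic factors that the allocation has balanced keeps their variance in the error term and makes the interval too wide. In a non-inferiority trial, a wider interval directly costs power.

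**Working it through.** **Inputs from the protocol.** Margin 0.5 (Figure 3 legend). SD of CRQ domain scores 0.8 to 1.2, with 0.8 used for planning; 44 evaluable per group; one-sided 5%; 90% power; 15% drop-out (Sample size). Two-sided 95% confidence interval for the decision (Effectiveness).

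**Assumed.** The correlation r between baseline and two-week CRQ is not given; 0.3, 0.5 and 0.7 are shown. The SD is taken as equal at both times. The variance formulas are large-sample and ignore the small cost of estimating the covariate coefficients.

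**The plan's own figure.** n = (1.645 + 1.282)² × 2 × 0.8² / 0.5² = 43.9, so 44 per group; 44 / 0.85 = 51.8, so 52 per group and 104 in total. Both stated figures reproduce. The SD used is that of scores, so it fits the follow-up comparison. It equals the change-score SD only if r = 0.5.

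**Gap between raw and change-score estimates.** Change difference = follow-up difference − baseline difference. The baseline difference has SD 0.8 × √(2/44) = 0.171, and 0.171 / 0.5 = 0.34 of the margin. At SD 1.2 it is 1.2 × √(2/44) = 0.256.

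**Variance relative to raw follow-up.** Raw 1; change 2(1 − r); ANCOVA on baseline 1 − r². Since 1 − r² = (1 − r)(1 + r), ANCOVA never exceeds either of the others for r between 0 and 1.

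**Half-width and power** at 44 per group, SD 0.8. Half-width = 1.96 × 0.8 × √(v × 2/44), where v is the relative variance. Power = Φ(0.5 / (0.8 × √(v × 2/44)) − z), with z = 1.96 for the 95% interval or 1.645 for one-sided 5%.

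| | r = 0.3 | r = 0.5 | r = 0.7 |
|---|---|---|---|
| Relative variance, change | 1.40 | 1.00 | 0.60 |
| Relative variance, ANCOVA | 0.91 | 0.75 | 0.51 |
| Half-width, raw | 0.334 | 0.334 | 0.334 |
| Half-width, change | 0.396 | 0.334 | 0.259 |
| Half-width, ANCOVA | 0.319 | 0.290 | 0.239 |
| Power with 95% interval: raw / change / ANCOVA | 83 / 70 / 87% | 83 / 83 / 92% | 83 / 97 / 98% |
| Power at one-sided 5%: raw / change / ANCOVA | 90.1 / 79.7 / 92.3% | 90.1 / 90.1 / 95.9% | 90.1 / 98.4 / 99.3% |
| n per group for 90% power at one-sided 5%: raw / change / ANCOVA | 44 / 62 / 40 | 44 / 44 / 33 | 44 / 27 / 23 |

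**How the verdict can turn** (illustration, r = 0.5, interval minus continuous). Suppose the raw difference is −0.10 and interval patients start 0.17 higher.

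- Raw lower limit: −0.10 − 0.334 = −0.434, which clears −0.5.
- Change: −0.10 − 0.17 = −0.27; lower limit −0.27 − 0.334 = −0.604, which fails.
- ANCOVA: −0.10 − 0.5 × 0.17 = −0.185; lower limit −0.185 − 0.290 = −0.475, which clears.

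**How often** (200,000 simulated trials per setting, 44 per group, 95% interval rule):

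| Verdicts disagree | r = 0.3 | r = 0.5 | r = 0.7 |
|---|---|---|---|
| Raw vs change, no true difference, SD 0.8 | 25% | 20% | 17% |
| Raw vs change, no true difference, SD 1.2 | 31% | 34% | 39% |
| Raw vs change, true deficit 0.25, SD 0.8 | 25% | 29% | 38% |
| Raw vs ANCOVA, no true difference, SD 0.8 | 6% | 11% | 15% |

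With the true deficit exactly at the margin (SD 0.8), each estimate alone falsely declares non-inferiority in about 2.5% of trials. The chance that at least one of the three does so is 4.6% to 5.1%, for r from 0.3 to 0.8.

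**The case against.** Read literally, the decision rule names change scores and nothing else, and Figure 3 agrees, so the verdict could be called fixed and the fault merely one of labels. That reading is fair. But it makes the primary-analysis label wrong, and it ties the decision to an estimate whose power falls below the planned 90% if r is under 0.5.

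The protocol also keeps analysts blind to group identity and has two manuscripts agreed before the code is broken. This limits biased interpretation. It does not say which of two conflicting intervals governs, and coded groups can still give conflicting results.

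Several limits on the size of the problem stand:

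- Under randomisation all three estimates target the same mean difference, so no bias is shown. Even the best of three has a false-positive rate of about the one-sided 5% used for planning, although that is about twice the 2.5% implied by the 95% interval.
- The power loss depends on an r that the protocol does not give. Between change scores and ANCOVA it is 17 points at r = 0.3 and about one at r = 0.7.
- The 83% for raw scores reflects a separate mismatch between a 95% interval and planning at one-sided 5%. At the planned level, raw scores have the stated 90%.
- The SD of 0.17 for the baseline difference is probably an upper bound, because balancing HADS should remove some CRQ imbalance.
- The extra gain from the minimisation factors is not quantified. Leaving them out errs on the conservative side.

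An unadjusted primary analysis with an adjusted supporting one is a valid design. It is not a reason to leave two estimates competing for the same decision.

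**Conclusion.** The concern holds and should be fixed before analysis. The protocol contradicts itself on which estimate carries its main conclusion. With no true difference, the two candidates would disagree in roughly one trial in six to one in four at SD 0.8, and in about 31% to 39% at SD 1.2, for r between 0.3 and 0.7.

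The raw analysis also carries more variance than the ANCOVA already planned: the ANCOVA variance is 9%, 25% and 49% lower at r = 0.3, 0.5 and 0.7. The contradiction and the ordering of precision do not depend on r; the percentages do. They also rest on equal SDs at both times and on treating baseline CRQ as unbalanced by the allocation. The stated sample size is not shown to be wrong by this point.

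**What to change.** Name one estimate as both the primary analysis and the basis of the non-inferiority rule. The best choice is the ANCOVA of the two-week CRQ score with baseline CRQ and the four minimisation variables as covariates.

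- Apply the 95% interval rule to its adjusted difference in both the intention-to-treat and per-protocol sets.
- Reword the decision rule and the Figure 3 legend so that they refer to this adjusted difference.
- Keep the raw follow-up and change-score differences as descriptive or sensitivity results, and state that they do not decide.
- Do the same for the six-minute walk, with baseline walking distance as the baseline covariate and the protocol's ± 45 m boundary.

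The cost is analysis wording only. The model is already planned and its covariates are already collected, so no patients or assessments are added. The one restriction is on which result may be called primary.
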